## Abstract

**Background:**

Depressive symptoms are common in veterans, and the presence of these symptoms increases disability as well as suicidal thoughts and behaviors. However, there is evidence that these symptoms often go untreated. Intervening before symptoms become severe and entrenched is related to better long-term outcomes, including improved functioning and less disease chronicity. Computer-delivered interventions may be especially appropriate for those veterans with mild to moderate depressive symptoms, because these interventions can require fewer resources and have lower barriers to access and thus have potential for wider reach. Despite this potential, there is a dearth of research examining computerized interventions for depressive symptoms in veteran samples.

**Objective:**

The aim of this study is to evaluate the efficacy of Deprexis (GAIA AG), a computerized intervention for depressive symptoms and related functional impairment.

**Methods:**

Veterans will be recruited through the US Department of Veterans Affairs electronic medical record and through primary care and specialty clinics. First, qualitative interviews will be completed with a small subset of veterans (n=16-20) to assess the acceptability of treatment procedures. Next, veterans (n=132) with mild to moderate depressive symptoms will be randomly assigned to the fully automated Deprexis intervention or a treatment-as-usual control group. The primary outcomes will be self-reported depressive symptoms and various dimensions of psychosocial functioning.

**Results:**

This project was funded in May 2024, and data collection will be conducted between October 2024 and April 2029. Overall, 4 participants have been recruited as of the submission of the manuscript, and data analysis is expected in June 2029, with initial results expected in November 2029.

**Conclusions:**

This study will provide initial evidence for the efficacy of self-guided, computerized interventions for depressive symptoms and functional impairment in veterans. If effective, these types of interventions could improve veteran access to low-resource psychosocial treatments.

**Trial Registration:**

ClinicalTrials.gov NCT06217198; https://www.clinicaltrials.gov/study/NCT06217198

**International Registered Report Identifier (IRRID):**

PRR1-10.2196/59119

## Introduction

### Background and Rationale

Depression is the leading cause of disability worldwide [1], and those diagnosed with major depressive disorder (MDD) are up to 7.6 times more likely to die by suicide compared to the general population [2]. Depressive symptoms are associated with severe and chronic impairment in occupational and social domains [3], decreased quality of life [4], and adverse physical health outcomes [5]. Depression is a significant problem for US military veterans, with 13% of post-9/11 war veterans meeting criteria for current MDD [6] and 46.5% of female veterans and 36.3% of male veterans meeting criteria for lifetime MDD [7]. The high prevalence of depressive symptoms in veterans not only has negative ramifications for social and interpersonal functioning, occupational participation, and quality of life [8] but also markedly increases the risk for suicide. On average, 543 veterans die by suicide each month [9], and MDD is the second most important predictor of veteran suicide among all recorded mental health diagnoses [10]. Depressive comorbidity among veterans with posttraumatic stress disorder (PTSD) compared to PTSD alone is also associated with elevated rates of disability in cognitive (Cohen *d*=1.03) and mental health (Cohen *d*=1.49) domains. Veterans with comorbid PTSD and MDD also reported decreases in quality of life (Cohen *d*=0.84) and a 2-fold risk of suicide compared to those with PTSD alone [11]. Given the functional impairments and elevated suicidal risk associated with depressive symptoms, it is essential to provide veterans with timely and appropriate intervention.

Addressing depression before the symptoms become severe and entrenched could substantially improve outcomes. Even mild to moderate and subthreshold depressive symptoms are associated with significant disease burden, including increases in disability and mortality and decreases in quality of life [12]. The rates of transition to MDD for individuals with subthreshold depressive symptoms are exceedingly high both in the short term [13] and long term [14]. When subthreshold symptoms progress to MDD, symptoms become chronic in the vast majority of cases, with 85% of individuals with MDD experiencing recurrent episodes even after receiving specialty mental health treatment [15]. Evidence suggests that interventions targeted at individuals with mild to moderate symptoms, including those with subthreshold symptoms of MDD, are effective in restoring functioning and preventing the progression to severe disease [16].

Although depressive symptoms often go undetected at mild to moderate or subthreshold levels in community settings [17], depression symptom screenings are routinely performed on a population level at US Department of Veterans Affairs (VA) facilities. This provides a key opportunity to identify veterans with depressive symptoms, even before these symptoms reach the diagnostic threshold, allowing for rapid and high-quality intervention. Patient preference studies indicate that individuals with depressive symptoms prefer to receive psychotherapy over medication [18]. Although the VA has made significant strides in improving access to psychotherapy, including through the expansion of primary care–mental health integration [19], many veterans still struggle to access adequate psychotherapy. Research shows that the majority of veterans (61%) with diagnosed mental health disorders only attend 1 session of psychotherapy [20]. Shame and stigma around depressive symptoms and seeking mental health treatment, as well as difficulties attending mental health treatments due to a lack of time or transportation, are known barriers to adequate and timely intervention and care [21]. Although the expansion of virtual mental health care (ie, telehealth) within VA facilities is effective at overcoming certain logistical barriers to treatment, telehealth is as resource intensive as traditional face-to-face psychotherapy, and access is dependent on provider availability. Furthermore, VA telehealth services might be less appropriate for individuals with mild to moderate symptoms, whose symptom severity level might not merit individual psychotherapy, but who would nonetheless benefit from help. Thus, despite increased detection of depressive symptoms and an identified need for intervention, a significant treatment gap exists.

Internet-delivered interventions are well positioned to fill this treatment gap because these interventions are low cost, easily accessible, and scalable. When compared to telehealth or traditional face-to-face mental health care, internet-delivered interventions could alleviate veterans’ stigma concerns and provide increased flexibility of access in the presence of competing demands of work and childcare. Positive experiences with internet-delivered interventions could also facilitate the eventual transition to traditional mental health care if needed [22]. Meta-analyses of results from community samples provide evidence for the effectiveness of internet-delivered interventions for depressive symptoms, including acceptance and commitment therapy [23], cognitive behavioral therapy [24,25], and mindfulness-based approaches [26].

Deprexis (GAIA AG) [27,28] is an internet-delivered intervention that integrates acceptance and commitment therapy, cognitive behavioral therapy, and psychodynamic and mindfulness-based approaches. The program consists of 10 core modules targeting depressive symptoms and associated functional impairment. Engagement with content is completely self-guided, and the program is accessed remotely. A randomized controlled trial (RCT) of Deprexis in a general population sample found that it was effective in reducing depressive symptoms, improving well-being, and decreasing disability [29]. Despite these positive results in the general population, it is unknown whether Deprexis is an effective treatment for veterans with depressive symptoms, given the unique composition of the veteran population in terms of gender ratio, barriers to treatment, the severity of comorbid conditions, and sociodemographic characteristics. Furthermore, there is a need to understand whether this low-intensity, internet-delivered treatment for depression also addresses functional impairments in veterans. A critical gap in the field is testing the effects of evidence-based mental health interventions on recovery outcomes. The primary goal in previous trials was to test the effect of Deprexis on depressive symptoms. Although improvements in functional domains after Deprexis treatment have been reported [29], the conducted assessments did not span the full range of functional outcomes. There is a need to centralize the assessment of psychosocial functioning in mental health delivery research generally and the study of Deprexis specifically.

### Aims

Deprexis has not yet been rigorously evaluated with a veteran population in a VA medical center setting. This study aims to fill this critical gap in the literature by testing whether Deprexis is acceptable and effectively decreases depressive symptoms and improves functional outcomes in veterans (N=152) presenting for VA health care with mild to moderate depressive symptoms. The objective of aim 1 is to assess perceptions, needs, and preferences as they relate to Deprexis through conducting posttreatment assessment interviews with veterans (n=16-20) and identify the components that improve veterans’ experience and uptake of Deprexis. The results obtained in aim 1 will be used to inform the rollout of RCT procedures under aim 2. Aim 2a involves completing an RCT comparing an 8-week course of Deprexis to a treatment-as-usual (TAU) control condition. We hypothesize that veterans engaged in Deprexis will show improvements on measures of functioning and decreases in depressive symptoms compared to the TAU control group. To generate hypotheses for future study, the objective of exploratory aim 2b will be to examine whether demographic variables, baseline psychopathology, credibility, and Deprexis use moderate treatment effects on the primary outcomes.

## Methods

### Trial Design

This study is an individually randomized, parallel, 2-group therapy trial. A total of 132 veterans will be randomized in a 1:1 fashion to either a Deprexis intervention or a TAU control group.

### Study Setting

Recruitment will take place within the VA Central Texas Healthcare System. All assessment and intervention components will be completed remotely through Qualtrics (Qualtrics International Inc) [30] and the Deprexis website, respectively.

### Eligibility Criteria

Potential participants include all veterans irrespective of sex or gender and of all ages and races and ethnicities who (1) are able to comprehend and sign the informed consent form; (2) have reliable access to the internet and a computer, tablet device, or smartphone; (3) exhibit mild to moderate (not very severe) levels of depression (Quick Inventory of Depressive Symptomatology–Self-Report [QIDS-SR] [31] score between 6 and 20 at the time of screening); and (4) are stable on psychotropic medications (defined as no medication change in the 30 days before study entry). The last criterion is included to ensure that the symptoms evaluated during the pretreatment assessment are due to underlying psychiatric conditions and not because of starting or stopping medications. Veterans will be excluded from study participation if they (1) endorse any positive symptoms of a psychotic disorder (assessed via the Psychiatric Diagnostic Screening Questionnaire [PDSQ] [32]), (2) screen positive for bipolar I disorder (assessed via the Mood Disorder Questionnaire [33]), or (3) report current suicidal risk (assessed via Beck Depression Inventory–Second Edition [BDI-II] item 9 [34]).

### Recruitment

For this study, veterans presenting with mild to moderate symptoms of depression will be recruited. Recruitment letters, including a link to the Qualtrics survey, will be sent out by US mail to veterans identified through the medical record who screen positive on the Patient Health Questionnaire (PHQ)-2 clinical reminder screen (a score of ≥3). The initial eligibility criterion is purposefully broad (ie, a positive PHQ-2 screen vs a positive PHQ-9 screen) because we do not want to exclude treatment-receptive veterans with mild depressive symptoms. Veterans’ telephone numbers will be obtained from the medical record, and a research technician will contact veterans by telephone to ensure that they have received their letters, answer any questions, and provide them with a link to the Qualtrics survey if needed. Flyers at VA primary care and medical specialty clinics will also be posted and distributed, and information about the study and participant inclusion and exclusion criteria will be provided to VA primary care providers.

### Intervention Description

Deprexis is an internet-delivered treatment for depressive symptoms and related functional impairment. The intervention draws from various theoretical frameworks and consists of 12 modules: 10 core content modules, an introductory module, and a summary module. Deprexis, which is designed to be interactive involves answering questions and learning techniques and concepts through instruction and examples. Deprexis uses a software technology (Broca) that tailors content dynamically to the users’ responses, resulting in a simulated conversational flow. To increase motivation, Deprexis features symptom tracking, with accompanying graphical and text feedback, worksheets and summaries in printable format, audio recordings, and illustrations. The content focuses on improving depressive symptoms (eg, cognitive restructuring of depressogenic thoughts) and decreasing functional deficits associated with depressive symptoms (eg, behavioral activation, interpersonal skills, and healthy lifestyle choices). The program is self-paced, and every module takes between 10 and 60 minutes to complete. Participants are provided a free Deprexis voucher and will access the intervention through the Deprexis website. Textbox 1 [27] presents an overview of session content, while Figure 1 depicts a Deprexis sample presentation.

Deprexis module content.
**Introduction**
Overview of the Deprexis program; psycho-education about the relationships among thoughts, feelings, and behaviors; observing and accepting thoughts and feelings; mindfulness exercise; a worksheet to encourage regular program use
**Behavioral activation**
Exploring the relationship between activity and depressive symptoms; psycho-education on basic psychological needs (eg, need for competence and social relatedness); selecting and scheduling activities that satisfy basic psychological needs using a checklist and log; exploring and problem-solving barriers to completing activities
**Cognitive modification**
Psycho-education on automatic thoughts; exploring antecedents and consequences of automatic thoughts; common cognitive distortions; strategies for correcting cognitive distortions (eg, birds-eye view and a scientist’s perspective)
**Relaxation, physical exercise, and lifestyle modification**
Relationship between lifestyle habits (eg, sleep, exercise, and diet) and depression; instruction and practice of various relaxation exercises to help mitigate stress (eg, diaphragmatic breathing and visual imagery)
**Acceptance and mindfulness**
Illustrate the difficulty of controlling thoughts and feelings and the alternative of calmly accepting unwanted thoughts and feelings using metaphors and exercises; mindfulness exercises that promote acceptance (eg, leaves on a stream); clarifying values and taking value-consistent action
**Problem solving**
Strengthening problem-solving skills by defining problems in concrete rather than vague terms, setting achievable goals, generating a variety of potential solutions, evaluating solutions, implementing the chosen solution, and evaluating outcomes
**Childhood experiences**
Exploring difficult childhood memories and using coping skills such as expressive writing, acceptance, forming new positive memories, and forgiveness
**Interpersonal skills**
Psycho-education about the relationship between interpersonal functioning and depression; exploring different communication styles (eg, assertive, passive-aggressive, aggressive, and nonverbal communication); practicing communication techniques (eg, nonblaming communication)
**Positive psychology**
Psycho-education about positive psychology; focusing on strengths instead of deficits; fostering happiness by savoring positive experiences and identifying and fostering talents
**Dreamwork and an emotion-focused intervention (optional)**
Coping with distressing dreams (eg, keeping a dream journal and rewriting the ending of dreams); reconceptualizing dreams as a way for our brain to help us problem solve

**Figure 1 figure1:**
[figure not shown]
Deprexis sample presentation.

Veterans randomized to the control condition will have access to standard VA treatment resources, including mental health treatment (they will be provided with a list of available resources).

### Criteria for Discontinuing or Modifying Allocated Interventions

Veterans can choose to discontinue study involvement at any time without facing any consequences. We will actively monitor for any serious adverse events occurring during their study involvement. Modifications to intervention components or procedures may be made at the discretion of the principal investigator (PI; RP), pending approval from the institutional review board (IRB) and other relevant stakeholders.

### Strategies to Improve Adherence to Intervention Protocols

Adherence will be optimized using strategies from previous Deprexis trials. All veterans will be sent brief SMS text messages to increase engagement. These SMS text messages will target behavioral and cognitive processes that are known to maintain depressive symptoms and will include reminders to use the Deprexis program. Research staff will also have access to veterans’ real-time Deprexis use data, and based on this use data, short encouraging emails will be sent to them by research staff. These emails will range from acknowledging the veterans’ use of the Deprexis program to encouraging further engagement and addressing feelings of discouragement. Research staff will also reach out to veterans who have not activated their free Deprexis vouchers to provide technical support if needed. Study staff will initiate contact with veterans if there is no engagement with Deprexis over a 2-week period.

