#### Who Will Be Blinded?

The use of a TAU control condition precludes the blinding of participants and research staff. Confounds due to research staff not being blinded will be minimal because all assessment and intervention components will be completed remotely without research staff support. Given that we only use self-report measures, the involvement of research staff in responses will be very limited, and rater effects are unlikely.

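### The Deprexis arm gets depression-directed text messages and staff contact, so the trial tests a supported package, not the fully automated, self-guided program it names

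*Protocol article*

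**What the plan says.** All places are in the protocol article.

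- **Label of the intervention.** In the abstract (Methods), veterans will be "randomly assigned to the fully automated Deprexis intervention or a treatment-as-usual control group". Background and Rationale says: "Engagement with content is completely self-guided, and the program is accessed remotely".
- **Conclusion.** The abstract (Conclusions) says: "This study will provide initial evidence for the efficacy of self-guided, computerized interventions". The Discussion (Summary) likewise presents the trial as the first randomized trial of a self-guided, computerized intervention of this kind in veterans.
- **What is delivered.** Strategies to Improve Adherence to Intervention Protocols says: "All veterans will be sent brief SMS text messages to increase engagement". It then adds: "These SMS text messages will target behavioral and cognitive processes that are known to maintain depressive symptoms". The messages also carry reminders to use Deprexis. Staff see use data in real time and send emails based on it, some of them meant to deal with discouragement. Staff also contact veterans who have not activated their voucher, or who have not used Deprexis for 2 weeks.
- **Blinding.** Who Will Be Blinded? calls confounding from unblinded staff minimal because "all assessment and intervention components will be completed remotely without research staff support".
- **Control.** Under Intervention Description, controls have standard VA resources and a list of them.

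**The concern.** The adherence section and the blinding section describe different trials. One has staff watching use, writing to participants and calling on those who lapse. The other has no staff support and relies on that to set aside a source of bias.

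What is at stake is what a positive result would mean. The rationale is low-resource care: a program that can be offered widely, with face-to-face therapy kept for severe cases. If part of the benefit comes from depression-directed messages or from staff contact, the result does not show that the program alone would deliver it. All outcomes are self-reported by participants who know their arm, so encouraging contact given to one arm only is a plausible contributor to any difference.

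The message sentence adds a second problem, because it does not say which arm it covers. A control group that received the messages would no longer be the usual-care group that the protocol describes.

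**Working it through.** No figure in the plan depends on this point. The check sets the sections side by side.

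**1. Are the added components part of Deprexis as described?** Intervention Description lists modules, tailored content, symptom tracking with feedback, worksheets, audio and illustrations. Text messages, staff emails and staff outreach are not listed. They appear only under the adherence strategies.

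**2. Are the messages only reminders?** No. Their stated target is the processes that maintain depression, and reminders are an additional element.

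**3. Which arm can receive each component?**

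| Component | Trigger | Deprexis | TAU |
|---|---|---|---|
| Text messages | none stated; no arm named | yes | unclear |
| Staff emails | Deprexis use data | yes | not possible |
| Outreach | voucher not activated, or 2 weeks without use | yes | not possible |
| Assessment reminders and calls (Plans to Promote Participant Retention) | assessment due or missed | yes | yes |

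The last row is study contact in both arms, but it concerns questionnaires and not mood or engagement.

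**4. What does the comparison estimate?** Write P for the effect of the program, M for the messages and S for staff emails and outreach, and assume for simplicity that they add.

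- Messages to the Deprexis arm only: difference = P + M + S, against TAU.
- Messages to both arms: difference = (P + M + S) − M = P + S, against TAU plus messages.

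Neither equals P. A two-arm trial gives one difference and cannot split it.

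**5. Does any planned analysis separate the parts?** Outcomes lists frequency of study support as an exploratory moderator. Support that depends on Deprexis use arises after randomization and exists in one arm only, so this analysis cannot separate program from support.

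**6. Does the blinding argument hold?** It makes two claims. The claim that staff do not score outcomes stands, because all measures are self-report. The claim that there is no staff support during the intervention conflicts with step 3, so the inference that confounding is minimal loses that premise.

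**The case against.** The best defence is that nothing is hidden. The adherence strategies are described openly and are said to come from previous Deprexis trials. Working through content unaided is compatible with being reminded to log in, so the self-guided description in Background and Rationale can stand for the content itself. The limitations in the Discussion (Summary) admit that use is monitored closely, that this may not be feasible in clinics, and that automating reminders is a future step. They also concede that TAU is a weak comparator. Most of this stands. The limitations, however, treat monitoring as a feasibility matter. They do not mention the depression-directed message content or the question of attribution, and they leave the blinding statement uncorrected.

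It is also fair that the message sentence, placed under adherence and mentioning Deprexis reminders, most naturally means the Deprexis arm. That reading is accepted here; the wording still needs to say so.

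A reader might infer two stronger things. The first is that the comparison is broken and supports no conclusion. The documents do not bear this out: it remains a valid randomized test of the supported package.

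The second is a calculable loss of power or share of the effect. The documents give no size for the messages or contacts, so any such figure only restates an assumption. Even if controls received the messages, only M would cancel, because emails and outreach cannot reach them. A two-sided power calculation would also mix in a separate matter. The stated total of 102 at d = 0.50 matches a one-sided t test (50.15 per arm, rounded up to 51; 2 × 51 = 102). A two-sided test needs 63.77, rounded up to 64 per arm, or 128.

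**Conclusion.** The point holds as a contradiction between sections and a limit on what may be concluded. The label of full automation and the statement of no staff support cannot stand beside the adherence section. The trial can show whether Deprexis with text messages and staff engagement support does better than TAU. It cannot show how much of that is due to the self-guided program.

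No numerical size can be given. The conclusion rests on the adherence strategies being delivered as written, on outcomes being unblinded self-report, and on the messages going to the Deprexis arm only. If they went to both arms, the program would still not be isolated, and the comparator would be TAU plus messages. The change is worth making because it alters the claim and costs almost nothing.

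**What to change.** 1. **Adherence section:** replace the opening of the message sentence with *veterans randomized to Deprexis*, the reading its context supports.
2. **Intervention Description:** declare the text messages, staff emails and outreach part of the tested intervention.
3. **Abstract (Methods):** remove the description of the intervention as fully automated.
4. **Abstract (Conclusions) and Discussion (Summary):** restate the claim as Deprexis with text-message and staff engagement support versus TAU. The Objective and Aims use neither disputed term and need no change on this account.
5. **Who Will Be Blinded?:** say that staff do contact the Deprexis arm and that this, with unblinded self-report, is a possible source of bias. Keep the point that staff do not rate outcomes.
6. **Reporting:** give the number of staff contacts by arm. Support frequency is already a planned variable, so little extra collection should be needed.

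Message content does not need to change; declaring it is enough. The cost is protocol wording and a narrower claim, with no extra participants. Only 4 participants had been recruited when the article was submitted.
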